### Sample size

Initially, the study was expected to include between 30 and 50 ICUs of the IMPACTO-MR platform, with an expected sample size of 30,000 patients (
Figure 1S - Supplementary Material
). However, owing to feasibility issues and restrictions on the study’s budget provided by the Brazilian Ministry of Health after December 31, 2023, the sample size was recalculated considering possible variations in the number of clusters, cluster size, and data from the IMPACTO-MR database to estimate the baseline rate of HCAIs. Therefore, by including 12,600 patients (21 clusters with a mean of 600 patients each) with a baseline rate of 6 HCAIs per 1,000 patient-days and a between-cluster variance of 0.6, our study will be able to detect a 9% (relative risk of 0.91) reduction in the incidence of HCAIs, with 80% power and an alpha of 5% (
Figure 2S - Supplementary Material
). Details are provided in the
Supplementary Material
.

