### Statistical analysis

The main analysis will follow the intention-to-treat framework with patient-level data. Each patient will be analyzed according to the group (CHG or soap and water bath) assigned to the ICU at admission, irrespective of the length of stay and the number of days the patient received each intervention. Patients whose stay crosses into another treatment period will be analyzed according to their initial assignment, and patients admitted during the washout period will not be included in the intention-to-treat analysis. We will perform a sensitivity analysis including only patients admitted and discharged during the same intervention period.

The primary outcome of HCAI incidence per 1,000 patient-days will be analyzed using a Poisson generalized mixed linear model with allocation group, study period, and the interaction of allocation group and study period as fixed effects and center as a random effect. Other possible distributions and models might be considered according to the variable’s behavior. We will use the same model to evaluate the incidence per 1000 patient-days of each specific HCAI (CLABSI, VAP, and CAUTI), rates of positive microbiological cultures for multidrug-resistant pathogens, and antibiotic use. Mortality will be assessed using survival and logistic regression models, taking the center, allocation group, and study period as random effects and the interaction of the allocation group and study period as a fixed effect. Generalized mixed linear models with appropriate distributions will be utilized for other outcomes. Preplanned subgroup analyses will be conducted according to the following characteristics: surgical
*versus*
nonsurgical admission, SAPS 3 score ≤ 40
*versus*
> 40, public
*versus*
private ICU, and ICU length of stay ≤ 7
*versus*
> 7 days.

No adjustments for multiplicity will be performed, and a 2-sided p value of less than 0.05 will be considered statistically significant. All the statistical analyses will be performed using R software (R Foundation for Statistical Computing, Vienna, Austria; https://www.R-project.org/).^(
30
)^

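### The primary Poisson model has centre as its only random effect, so to the extent that an ICU's rate varies between its periods the standard error is too small and type I error exceeds 5%

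*Protocol article*

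**What the plan says.** The protocol article's Statistical analysis section states: "The main analysis will follow the intention-to-treat framework with patient-level data". The primary outcome, HCAIs per 1,000 patient-days, "will be analyzed using a Poisson generalized mixed linear model". Its terms are group, study period and the group-by-period interaction, which enter "as fixed effects and center as a random effect". Significance is judged by this rule: "a 2-sided p value of less than 0.05 will be considered statistically significant". The only qualifier is "Other possible distributions and models might be considered according to the variable’s behavior", which names no alternative and no condition for using one. The same model is to serve the individual HCAIs, MDR culture rates and antibiotic use.

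The Design section makes the ICU the randomised unit, crossing over between baths after periods of 3 to 6 months. The Sample size section gives 21 clusters averaging 600 patients, 6 HCAIs per 1,000 patient-days and "a between-cluster variance of 0.6", without a scale. The article states no within-ICU, between-period variance or correlation.

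**The concern.** In a cluster crossover, the unit that receives a treatment is the ICU-period. Two patients in the same ICU and period usually resemble each other more than two patients in the same ICU months apart, because outbreaks, staffing and case mix change. A centre intercept alone assumes that an ICU's underlying rate is constant across its periods, apart from shifts shared by every ICU. The fixed period and interaction terms are common to all ICUs, so they cannot absorb one unit's own change.

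The article gives reason to expect such changes. Its Discussion refers to effects of the intervention on the ICU's microbiology, accepts that a longer washout would have been preferable, and reports that centres started at different times.

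At stake are the primary p-value and confidence interval. The error runs towards false positives, and the decision concerns a policy for whole ICUs.

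**Working it through.** **Inputs from the article.** 21 ICUs; 600 patients per ICU in total (21 × 600 = 12,600); 6 HCAIs per 1,000 patient-days; variance 0.6; two-sided 5% level.

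**Assumptions, because the article does not give them.** 7 patient-days per patient; two periods per ICU; equal ICU sizes; normal log-rate effects; 0.6 read as the total variance of the log rate, part of it between centres and part (s²) centre-by-period.

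**Events per ICU-period.** k = (600 / 2) × 7 × 0.006 = 12.6.

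**Approximate formula.** One ICU-period's log rate has variance of about 1/k + s². The centre-only model counts only 1/k. It therefore understates the variance of the log rate ratio by the factor (1/k + s²) / (1/k) = 1 + k·s², and the actual two-sided level is

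2 × [1 − Φ(1.96 / √(1 + k·s²))].

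For s² = 0.06: 1 + 12.6 × 0.06 = 1.756; √1.756 = 1.325; 1.96 / 1.325 = 1.479; level = 13.9%. The formula treats all ICUs as having equal rates. When rates differ widely, the high-rate ICUs carry most of the events and the inflation is larger, so simulation is needed.

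**Simulation.** 1,000 null trials per row; random-intercept Poisson model fitted by adaptive quadrature. The plan's nominal 5% is reproduced when s² = 0.

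| s² | share of 0.6 | between-period correlation | formula | simulated type I error | mean model SE | true SD of log RR |
|---|---|---|---|---|---|---|
| 0 | 0% | 1.00 | 5.0% | 5.2% | 0.090 | 0.091 |
| 0.03 | 5% | 0.95 | 9.5% | 10.9% | 0.090 | 0.109 |
| 0.06 | 10% | 0.90 | 13.9% | 17.2% | 0.090 | 0.129 |
| 0.12 | 20% | 0.80 | 21.6% | 25.1% | 0.090 | 0.158 |

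The model's standard error does not move while the true spread grows. Monte Carlo error is about 0.7 points near 5%. A second simulation with a conditional Poisson fit gave 4.8%, 11.4%, 17.4% and 25.1% for the same rows.

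**Sensitivity to the assumptions.**
- Stay: at s² = 0.03 and 0.12, type I error is 10.5% and 21.9% with 5 days per patient, and 14.9% and 34.9% with 10 days.
- Four periods per ICU, same total events: roughly 8% to 19% for s² from 0.03 to 0.12.
- 0.6 as a variance of the rate per 1,000 patient-days: the log variance is about 0.6 / 6² = 0.017. Type I error is then about 5% to 7% for between-period correlations of 0.9 to 0.5.

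**Does the remedy work?** A paired t-test on within-ICU log rate differences, adjusted for sequence (21 − 2 = 19 df), held type I error between 3.6% and 6.9% in every scenario.

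**The case against.** The strongest reply is that the inflation depends on a quantity the article never states. With no centre-by-period variation the planned model holds its level, and with 0.6 on the rate scale the excess is small or absent. The number of periods is not certain either: the figure of allocation sequences is not available here, and the section on the soap and water bath mentions washout periods in the plural. More periods reduce the inflation. The contrast tested also matters. If it were the reference-coded group coefficient, which is the period-1 effect, type I error was 7.0% to 12.8% for s² from 0 to 0.30, a different pattern from the table. All of this stands, and it is why the size is given as a range.

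The sponsor could also point out that the Discussion promises to account for the time of each intervention, and that the article leaves room for other models. Neither point answers the concern. A period term shared by all ICUs removes only common shifts, and a statement that other models may be considered commits to nothing.

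Three stronger readings are tempting but unsupported.
- A reader might infer that the sample size ignored between-period variation because only one variance is named. The details are in supplementary material not shown, so this cannot be concluded.
- A reader might infer that a Poisson model cannot accommodate repeat infections in one patient. It can, since a count may exceed 1.
- A reader might take a negative binomial as the cure. At patient level it allows extra variation between patients but still ignores their correlation within an ICU-period.

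**Conclusion.** The point holds in conditional form. The article fixes a primary model without a centre-by-period component, and this makes the standard error too small to the extent that ICU rates vary between periods. A reader might infer that type I error is well above 5% as a matter of fact. The article does not support that, because it gives neither the between-period variance nor the scale of 0.6.

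Under the main assumptions (7 days, two periods, log scale), a between-period correlation as high as 0.95 already about doubles the nominal level. At 0.90 and 0.80 the intervals would need to be about 1.4 and 1.8 times as wide (0.129 / 0.090 and 0.158 / 0.090). Under the most favourable reading there is little or no inflation. Zero variation within ICUs is nevertheless the assumption that the planned model needs, and the article offers no support for it.

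**What to change.** Add a centre-by-period random effect to the primary model, (1|center) + (1|center:period), with period in that term meaning each ICU's own intervention period. Base the test and interval on small-sample degrees of freedom tied to the 21 to 23 ICUs. Alternatively, make the primary analysis a cluster-period analysis of within-ICU log rate differences. Use the same structure for the individual HCAIs, MDR culture rates and antibiotic use. The factor 1 + k·s² grows with the event count, so outcomes with more events per ICU-period are more exposed. If another count distribution is adopted, keep the centre-by-period term alongside it.

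The cost is one model term, a few lines of text and somewhat wider intervals. The Perspective section places database closure and analysis after the time of writing, so the change should be documented before outcomes are compared by group.

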### Randomization, allocation concealment, and blinding

Randomization was performed through cluster randomization with crossover, where the unit of randomization was the ICU. Randomization lists were generated by an independent statistician using R software.^(
30
)^ Randomization was performed by the coordinating center using a central online randomization system (RedCap^®^) on the day of each center’s activation. The intervention sequence was disclosed to the investigators only after all the center’s information was recorded in the online system.

This study is an open-label trial in which patients and investigators are not blinded to the study interventions. The visual aspect and smell of the 2% CHG solution prevents the blinding of patients and study personnel.

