### Perspective

Inclusion of patients in the CLEAN-IT trial ended on December 31, 2023. As we write the draft for this trial protocol, each center is finalizing data collection, and we expect the database to be closed for analysis in late March. A total of 23 centers participated in the CLEAN-IT trial. We expect to perform data analysis and have the results published by the second semester of 2024.

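### The primary analysis is a Poisson mixed model with only a centre random effect, which an open-ended sentence then allows to be replaced, so the primary p-value is not tied to one analysis that holds 5%

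*Protocol article*

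**What the plan says.** All references are to the protocol article.

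- **Statistical analysis, default.** The model stated for the HCAI rate over patient-days: "will be analyzed using a Poisson generalized mixed linear model with allocation group, study period, and the interaction of allocation group and study period". Those three terms are fixed; centre is random. The main analysis uses patient-level data. No term is named for extra variation between patients, or between periods within an ICU.
- **Statistical analysis, next sentence.** "Other possible distributions and models might be considered according to" the behaviour of the variable. No candidate models, diagnostic, threshold or order of fallback follow, and nothing says that the Poisson result will be reported regardless.
- **Statistical analysis, reach.** "We will use the same model to evaluate the incidence per 1000 patient-days of each specific HCAI", and also for multidrug-resistant cultures and antibiotic use.
- **Statistical analysis, decision rule.** "No adjustments for multiplicity will be performed, and a 2-sided p value of less than 0.05 will be considered statistically significant".
- **Randomization, allocation concealment, and blinding.** "This study is an open-label trial in which patients and investigators are not blinded to the study interventions". How the analysis dataset is handled is not described.
- **Perspective.** "Inclusion of patients in the CLEAN-IT trial ended on December 31, 2023". Centres were still finalising data collection: "we expect the database to be closed for analysis in late March".

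**The concern.** The behaviour of the outcome can be judged only from outcome data, and the sentence sets no limit on what may follow from that judgement. A two-sided 5% test keeps its error rate if the model is fixed, or is chosen without regard to the treatment comparison. The article secures neither, and in an open-label trial with enrolment over a reader could not later tell a change made for fit from one made for the result.

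The default matters more. Each patient can contribute CLABSI, VAP and CAUTI events, and device exposure differs between patients, so counts may well vary more than Poisson. The Discussion also raises ICU-level microbiological effects and staggered entry of centres, which make period-to-period changes within an ICU plausible. A Poisson model with only a centre intercept absorbs neither source, so its standard error would be too small. Whether that is repaired is left to discretion. The primary claim, and the rate outcomes that inherit the model, depend on it.

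**Working it through.** The article gives no error rate for this clause beyond the nominal 5%, so there is no figure to reproduce. The check asks what happens under no treatment effect.

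**Inputs from the article.** 6 HCAIs per 1,000 patient-days; 12,600 patients; 21 clusters in the Sample size section, 23 ICUs in Design; between-cluster variance 0.6 (scale not stated; taken as log scale in step 2).

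**Assumptions (not in the article).** Two periods per ICU. Step 1: mean stay 7 days, SD 9; ICU log-rate SD 0.5; gamma patient heterogeneity variance 0, 2 or 4. Step 2: mean stay 5, 7 or 10 days; ICU-by-period log-variance 0, 0.02, 0.05 or 0.10. Runs per setting: 2,000 to 3,000. The Monte Carlo standard error is about 0.4 points near 5% (√(0.05 × 0.95/3,000)) and 0.7 near 12% (√(0.12 × 0.88/2,000)).

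**Step 1. Poisson default, patient heterogeneity only (23 ICUs).**
Expected events: 12,600 × 7 × 0.006 = 529.
Variance relative to Poisson ≈ 1 + v × rate × E[stay²]/E[stay], with E[stay²]/E[stay] = (49 + 81)/7 = 18.57. Ignoring ICU differences:
- v = 2: 1 + 2 × 0.006 × 18.57 = 1.22
- v = 4: 1 + 4 × 0.006 × 18.57 = 1.45

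The simulation measured 1.24 and 1.49. The test then behaves as if its critical value were 1.96/√1.24 = 1.76 or 1.96/√1.49 = 1.61, so true rejection is about 7.8% or 10.8%.

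Simulated rejection, three separate sets of runs:
- v = 2: 8.2%, 8.3%, 9.2%
- v = 4: 11.5%, 11.1%, 12.3%
- v = 0: 4.6% and 5.1% (two sets)

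Once overdispersion is allowed for, the rates are 4.8% (v = 2) and 4.1% (v = 4); with a patient-robust standard error, 5.3% and 5.4%.

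**Step 2. Poisson default, ICU rates that vary between periods (21 ICUs, 300 patients per period, no patient heterogeneity).**
Mean count per ICU-period at 7 days: 300 × 7 × 0.006 = 12.6. Variance factor ≈ 1 + s² × 12.6 if ICUs are alike, or 1 + s² × 12.6 × e^0.6 = 1 + s² × 22.96 with between-ICU log-variance 0.6.

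| s² | Factor | Implied rejection | Simulated, 7 days | Simulated, 5 to 10 days |
|---|---|---|---|---|
| 0 | 1 | 5% | 4.6% | 4.3–5.0% |
| 0.02 | 1.25–1.46 | 8.0–10.5% | 9.2% | 8.7–11.5% |
| 0.05 | 1.63–2.15 | 12.5–18.1% | 15.2% | 12.6–21.8% |
| 0.10 | 2.26–3.30 | 19.2–28.0% | 24.2% | 22.2–32.1% |

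A fixed cluster-level t test on log rates held 3.8% to 5.5% in every setting.

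**Step 3. Is patient overdispersion alone enough?** No. A negative binomial model with an ICU effect only (v = 2) rejected in 7.9%, 12.4% and 19.9% at s² = 0.02, 0.05 and 0.10. A separate check gave about 7% to 11% at 0.02 to 0.05.

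**Step 4. What does the choice of model add?** Smallest p among four patient-level rate models (Poisson, quasi-Poisson, robust Poisson, negative binomial), against Poisson alone:
- v = 0: 5.4% vs 5.1%
- v = 2: 9.3% vs 9.2%
- v = 4: 12.6% vs 12.3%

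The addition is 0.1 to 0.4 points. A wider set adds logistic regression for any HCAI, first HCAI only, and two ICU-level t tests. At least one of its six analyses is then below 0.05 in 9.7%, 12.0% and 14.9% of trials (v = 0, 2, 4). Those extra analyses change the outcome or leave the patient level, and always taking the smallest p is a worst case.

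**The case against.** The strongest reply has four parts.

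1. **A trigger and a candidate list usually sit in the SAP, which is not shown.** This stands in part. An unseen SAP or supplement may hold the rule, and then citing it settles the matter. The point, however, is about a sentence that is present and reopens a named primary analysis. The article refers readers to supplementary material for outcomes and sample size, but not for this choice.

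2. **A reader might infer that the model will be chosen after the unmasked results have been seen.** The documents do not support that. Open label describes patients and investigators; it does not say who handles the analysis data or in what form. The database was still open. The behaviour of a variable most naturally means its distribution, which can be checked with arms pooled.

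3. **A reader might infer that trying several models pushes the error rate to 10% or 15%.** Step 4 shows otherwise for models that keep the stated outcome and the patient-level rate. The larger figures need a change of outcome or of analysis level, or come from the Poisson default itself. The article fixes incidence per patient-day and patient-level data, so reading the sentence as licence to replace them is the broadest possible reading.

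4. **Leaving Poisson can protect the error rate.** This is right. A prespecified dispersion test that switched to quasi-Poisson gave 4.1% to 4.7% with no ICU-by-period variance and 6.9% to 11.2% with it, below fixed Poisson wherever that variance was present. So deleting the sentence and keeping plain Poisson would not be enough.

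**Conclusion.** The point holds in a limited form. The article names a primary model that is anti-conservative under plausible extra variation, then leaves any move away from it to unstated discretion. Under the assumed patient heterogeneity the default rejects a true null in about 8% to 12% of trials. With ICU-by-period log-variance 0.02 to 0.10, and no patient heterogeneity, the figure is about 9% to 32%. With neither source it holds about 5%.

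These sizes rest on assumed stay, heterogeneity and period variance; the article gives no dispersion figure, so it cannot be said that the default will fail, or that the clause will be used. The documents give no sign that results by arm have been seen, and selection among patient-level rate models is a minor contributor. What is firm is that neither the named model nor the sentence after it guarantees the stated 5%. The matter is worth settling before the treatment comparison is run.

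**What to change.** Delete the sentence. Before allocation is attached to the outcome data, fix in a dated SAP:

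- **Primary analysis.** Number of HCAIs per patient with log patient-days as offset, in a negative binomial mixed model with a centre effect and an added ICU-by-period random effect, using a small-sample correction suited to 21 to 23 clusters. A cluster-level analysis of log rates is a simpler alternative, since it held about 4% to 5.5% in simulation. Choose one.
- **Primary estimate.** A single CHG/soap rate ratio, with a statement of how the group-by-period interaction is handled so that only one ratio can be read from the model.
- **Distribution check, if wanted.** Once, on data pooled over arms, with the candidates and criterion written down beforehand and the result dated.
- **Everything else.** Sensitivity analyses that cannot replace the primary p-value.

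If an existing SAP already does this, cite it in place of the sentence.

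The cost is one paragraph and no new data. The interval will be somewhat wider if extra variation is present, and the analysts give up the freedom to switch later.

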### Study outcomes

The primary outcome is the incidence of device-associated HCAIs (CLABSI, VAP, and CAUTI) during the ICU stay within each intervention period. The diagnosis of device-associated HCAIs is made according to the
*Agência Nacional de Vigilância Sanitária*
(ANVISA) definitions.^(
31
)^

The secondary outcomes are the incidence of each specific HCAI (CLABSI, VAP, and CAUTI) within each intervention period, rates of positive microbiological cultures for multidrug-resistant (MDR) pathogens within each intervention period, antibiotic use (measured by days of therapy [DOT] or defined daily dose [DDD]) within each intervention period, ICU and hospital length of stay up to 90 days, and ICU and hospital mortality up to 90 days.

Detailed information on the outcomes and study definitions is available in the
Supplementary Material
.

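### Antibiotic use and multidrug-resistant culture rates default to the infection Poisson model, with no term for overdispersion or centre-by-period variation and no rule for switching

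*Protocol article*

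**What the plan says.** For the primary outcome, the infection rate, the Statistical analysis section of the protocol article names a Poisson mixed model. Besides the main effects of allocation and period, its terms are "the interaction of allocation group and study period as fixed effects and center as a random effect". No patient-level, dispersion or centre-by-period term is named.

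The next sentence leaves room to change: "Other possible distributions and models might be considered according to the variable’s behavior". The text then continues "We will use the same model to evaluate the incidence per 1000 patient-days of each specific HCAI", and the list of outcomes covered by that sentence ends with "rates of positive microbiological cultures for multidrug-resistant pathogens, and antibiotic use".

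Under Study outcomes, one secondary outcome is "antibiotic use (measured by days of therapy [DOT] or defined daily dose [DDD]) within each intervention period" and another is "rates of positive microbiological cultures for multidrug-resistant (MDR) pathogens within each intervention period". Detailed definitions are left to the Supplementary Material, which is not shown.

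**The concern.** A Poisson model sets the variance equal to the mean. That is a reasonable start for device-associated infections, which the article puts at 6 per 1,000 patient-days. Antibiotic days behave differently. Some patients have none, treated patients have runs of consecutive days, and two drugs on one day count as two days of therapy. The independent unit is closer to the patient or the course than to the day. DDD is a ratio of doses and need not be a whole number, so a Poisson likelihood does not describe it.

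A random intercept for centre absorbs stable differences between units. It does not absorb extra variation between patients, or a change in prescribing within a unit from one period to the next. In a crossover the treatment contrast is made between periods within a centre, so that last component enters it directly.

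At stake is a secondary claim. With tens of thousands of antibiotic days, a chance difference could be reported as an effect of bathing on antibiotic use.

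**Working it through.** **Nothing to reproduce.** The article states no mean, variance, dispersion, treated share, DOT per patient or cultures per patient. From the article come 12,600 patients in 21 clusters of 600 on average, and the two-sided 5% level. Everything else below is an assumption.

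**Step 1: DOT, variation between patients.** Write DOT = X × L, where L is the stay and X is therapy days per day of stay, independent of L, with mean r and variance v. The true variance of the estimated rate divided by its Poisson variance is

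R = v·E[L²] / (r·E[L]) = (v/r) × E[L] × (1 + CV²),

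and the standard error is too small by √R. Assume a share p of patients treated; a share of the stay on therapy that follows Beta(3,1) (mean 0.75, mean square 0.6); agents = 1 + Poisson(a − 1), with mean a and mean square a² + a − 1; and log-normal stays with log-SD s, so that 1 + CV² = exp(s²). Then r = 0.75·p·a and v = 0.6·p·(a² + a − 1) − r².

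| p | a | mean stay, s | r | v | v/r | E[L](1+CV²) | R | √R | simulated |
|---|---|---|---|---|---|---|---|---|---|
| 0.9 | 1.1 | 5, 0.5 | 0.7425 | 0.156 | 0.210 | 6.42 | 1.35 | 1.16 | 1.16 |
| 0.7 | 1.2 | 7, 0.6 | 0.63 | 0.292 | 0.463 | 10.03 | 4.65 | 2.16 | 2.3 |
| 0.6 | 1.5 | 7, 0.8 | 0.675 | 0.534 | 0.792 | 13.28 | 10.5 | 3.24 | 3.2 |

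The last column is the empirical SD of the log rate ratio over the mean Poisson standard error. It comes from 60 simulated trials under no effect (21 units × 2 periods × 300 patients), with roughly 10% Monte Carlo error. Centre was fitted as fixed, without period terms.

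**Step 2: other case mixes.** With exponential stays (CV 1) of mean 5 to 10 days, 60–75% of patients treated on 85–90% of days and 0–30% on two drugs, simulated R is 2.4 to 11.8, so √R is 1.5 to 3.4. At 90% treated and 10% on two drugs, √R is 1.4 to 1.9. At 95% treated every day with one drug, v/r = 1 − 0.95 = 0.05 and R = 0.05 × 2 × mean stay. That gives 0.5 at 5 days and 1.0 at 10 days, so √R is 0.7 to 1.0 and there is no inflation.

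**Step 3: what a factor means.** The rejection rate under no effect is 2(1 − Φ(1.96/√R)): 9% at R = 1.35, 36% at 4.65 and 55% at 10.5.

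**Step 4: variation by centre and period.** Assume two periods per centre, a 7-day mean stay, 0.7 DOT per patient-day and no patient-level overdispersion. DOT per arm is 6,300 × 7 × 0.7 = 30,870, so the Poisson variance of the log rate ratio is 2/30,870 = 0.0000648. A centre-by-period log-SD τ adds 2τ²/21.

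- τ = 0.05 adds 0.000238; factor √(0.000303/0.0000648) = 2.2.
- τ = 0.10 adds 0.000952; factor √(0.001017/0.0000648) = 4.0.

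Adding τ = 0.1 or 0.2 to the last row of Step 1 gave simulated factors of 5.5 and 9.0.

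**Step 5: resistant cultures.** If a positive patient contributes a geometric number of positive cultures with mean m, the factor is about √(2m − 1): 1.0 at m = 1, 1.4 at 1.5, 1.7 at 2 and 2.0 at 2.5. Simulation gave 0.9, 1.25, 1.4 and 2.1. With τ = 0.2 and m = 1 it gave 1.2.

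**Step 6: would a dispersion check catch it?** In the second and third rows of Step 1, the square root of the Pearson dispersion was 1.81 and 2.36, below the factors needed, because long stays carry most of the variance. Adding τ = 0.2 to the third row moved it only from 2.36 to 2.42, while the true factor rose from 3.2 to 9.0.

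**The case against.** The strongest reply is that plain Poisson is a default and not a commitment. The sentence just before the extension to these outcomes allows another distribution according to how the variable behaves, and gross overdispersion is what that sentence is for. Details of a switch often sit in an analysis plan, which is not shown. This stands in part: the article does not bind the analysts to Poisson. But the clause names no trigger and no alternative, and Step 6 shows that an ordinary dispersion check can miss the centre-by-period component altogether. The model that the article does name is the wrong starting point for antibiotic use.

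A reader might infer that the standard errors are wrong by a factor of two or more as a matter of fact. The documents do not support that. No figure in them fixes dispersion, and defensible assumptions give values at or below 1 as well as above 3.

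A reader might also infer that repeat resistant cultures are counted. The article does not say so. De-duplication may be set in the Supplementary Material, and leaving it there is no fault.

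Two further points stand. Both outcomes are secondary, so the primary conclusion is untouched. And antibiotic and culture data come from prescription, pharmacy and laboratory records, so a patient-level remedy assumes that these can be linked to stays, as the stated patient-level analysis does.

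**Conclusion.** The point holds in a limited form. The article makes a Poisson model with a centre intercept the default for antibiotic use, where the variance is unlikely to equal the mean and where one of the two permitted metrics is not a count. Standard errors for antibiotic use are therefore likely too small, by an amount the documents cannot fix. Under the assumed case mixes the DOT factor runs from about 1 to about 3, with most scenarios near or above 2. A centre-by-period log-SD of 0.05 to 0.10 would alone give 2.2 to 4.0. For resistant cultures the concern is conditional: without repeats or centre-period variation the factor is about 1, and from repeats alone it reaches 2 only at about 2.5 positive cultures per positive patient. The change is worth making, but it bears on secondary claims only.

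**What to change.** Before database lock, which the Perspective section of the article places still ahead, state the following for these secondary outcomes.

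1. Make an overdispersed model the default: for example, a patient-level negative binomial with log patient-days as offset, the planned fixed effects kept, and a centre-by-period random effect added to the centre effect. Quasi-Poisson or a robust variance is an alternative. Given Step 6, a Pearson scale factor alone may under-correct, and a patient-level correction does not replace the centre-by-period term.
2. Name one antibiotic metric, DOT or DDD, as the main one. If DDD is used, analyse it with a model for continuous data, such as a mixed model on the log rate per centre-period. That form also serves if records cannot be linked to patients.
3. State whether repeat positive cultures count. If they do, use the same overdispersed model, or count the first positive per patient and pathogen.
4. Replace the open clause, for these outcomes, by a stated fallback and the condition that triggers it (for example, non-convergence).

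The cost is wider intervals, slightly more analysis work and a change of wording. No new data are needed, provided the records link to stays.
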